**Surveys**

***Baseline survey***

All participants will complete the baseline survey on the online survey platform (Wen Juan Xing, https://www.wjx.cn) at the time of registration. The baseline survey asks questions about their sociodemographic characteristics and sexual behaviors. After completing the survey, participants will receive 20 RMB (approximately 3 USD).

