***Follow-up survey***

All participants in the two arms will be asked to complete a brief online survey in four weeks. The follow-up survey will collect information about HCV testing frequency, time, location, method and result(s), and sexual behaviors within four weeks. Participants will receive 30 RMB (approximately 4 USD) for the follow-up survey.

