***Cost data***

We will use a micro-costing approach to identify, measure and value costs associated with the trial arms. The perspective will be from the health provider. This will include the start-up costs (e.g., packaging, personnel training), consumables (HCV self-testing kits, standard of care testing supplies), capital costs (office equipment, building rental), and personnel costs. The time horizon will be the duration of the trial.

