***Analysis plan***

*Primary outcome*

The primary outcome of HCV testing rate (including facility testing and self-testing) within four weeks will be evaluated using a difference in proportions. We are interested in determining whether there is an overall difference in HCV testing rates between the arms. There may be differences in patient populations across provinces (NGOs), so we will adjust for NGO in the analysis if there is evidence of such differences. The appropriate approach for such an analysis will depend on the frequency of testing in each arm. A model-based approach that uses identity link and binomial family can be used to adjust for NGO if the frequencies are not too extreme (e.g., too few testers in SOC). Otherwise, a stratified test like Cochran–Mantel–Haenszel can be used to produce an adjusted *P*-value. We may also consider pooling data from NGOs that have low frequencies in the SOC arm (e.g., 0 or 1 testers) prior to adjusting for NGO.

*Secondary outcomes*

Secondary outcomes of testing rates for HIV, chlamydia, and gonorrhea will be also be evaluated as a difference in proportions using the methods described for the primary outcome.

*Economic evaluation*

We will estimate the total unit and incremental unit cost for each arm in two trials. All costs will be categorized as startup costs, fixed costs and variable costs in this study. Start-up costs refer to the cost which are incurred in the process of study beginning, including coordination of survey platforms. Fixed costs refer to the cost which cannot change with the number of participants during the whole trial period, including venue and equipment cost. Variable costs refer to the cost which are expenses that vary with the number of participants used, including HCVST kits, postage and other consumables. We will calculate all the costs for each arm, and then this cost will be divided by the number of MSM tested and the number of newly detected HCV cases in each study arm to calculate incremental unit costs. In addition, the univariate, multivariate and probabilistic sensitivity analyses from a decision tree model will be used to examine uncertainty.

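### The start-up cost definition admits research-only survey set-up into unit costs that are meant to be from the health-provider perspective, with no stated split between research and delivery or between arms

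*Protocol*

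**What the plan says.** Two parts of the Protocol define what is costed.

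- **Cost data** fixes the viewpoint: "The perspective will be from the health provider". Its start-up examples are delivery items: "This will include the start-up costs (e.g., packaging, personnel training".
- **Analysis plan, Economic evaluation** sets three categories: "All costs will be categorized as startup costs, fixed costs and variable costs in this study". It then ties start-up cost to the study itself: "Start-up costs refer to the cost which are incurred in the process of study beginning, including coordination of survey platforms". The unit-cost rule follows: "We will calculate all the costs for each arm, and then this cost will be divided by the number of MSM tested", and likewise by the number of newly detected cases.

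No sentence removes research-only cost from the numerator, and none says how a cost shared by both arms is to be divided.

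The platform has mixed use. The eligibility and baseline survey runs on it (Study setting and population; Baseline survey), and the follow-up survey is also online. It is also one of two routes by which HCVST participants order a kit (HCVST arm) and by which participants in either arm upload results (HCV testing record and results).

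Secondary outcomes lists cost per person tested and cost per person diagnosed as results in their own right, next to an ICER between the arms.

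**The concern.** A provider offering HCV promotion or self-testing would not run the trial's baseline and follow-up questionnaires. Setting them up is a cost of doing research. A start-up definition based on the beginning of the study, with survey-platform coordination as its named example, therefore does not fit the provider perspective. To the extent that research-only cost enters, the reported unit costs describe running a trial and not delivering a test.

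The per-arm figures are exposed because their denominators are small and very unequal. The same amount charged to each arm is spread over a handful of SOC testers and many more HCVST testers. The Economic evaluation paragraph also labels these per-arm averages as incremental unit costs, so a reader could take the difference between them for the incremental comparison.

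**Working it through.** The Protocol states no cost figure, so there is none to reproduce. What can be checked is how a given research cost passes into the unit costs.

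**Inputs from the Protocol**
- 42 participants per arm in each trial (Sample size).
- SOC testing rate 10%, the design assumption (Sample size).
- HCVST testing rate 42%, which is 10% plus the detectable difference of about 32 points (Sample size), or 79%, the trial 1 pilot rate (Table S2).

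**Assumption, not in the Protocol**
- Research-only cost of 1,000 RMB per arm, 2,000 RMB in total. This is a scale unit and not an estimate.

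**Step 1. Testers = 42 × rate**
- SOC: 42 × 0.10 = 4.2
- HCVST: 42 × 0.42 = 17.64
- HCVST at the pilot rate: 42 × 0.79 = 33.18

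**Step 2. Addition per tester = research cost charged to the arm ÷ testers in the arm**

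| Split of 2,000 RMB (HCVST/SOC) | SOC, 10% | HCVST, 42% | HCVST, 79% |
| --- | --- | --- | --- |
| 50/50 | 1,000 ÷ 4.2 = 238 | 1,000 ÷ 17.64 = 57 | 1,000 ÷ 33.18 = 30 |
| 75/25 | 500 ÷ 4.2 = 119 | 1,500 ÷ 17.64 = 85 | 1,500 ÷ 33.18 = 45 |
| 100/0 | 0 | 2,000 ÷ 17.64 = 113 | 2,000 ÷ 33.18 = 60 |

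**Step 3. Change in the ICER = (HCVST share − SOC share) ÷ (HCVST testers − SOC testers)**
- 50/50: (1,000 − 1,000) ÷ 13.44 = 0
- 100/0 at 42%: 2,000 ÷ 13.44 = 149 RMB per additional person tested
- 100/0 at 79%: 2,000 ÷ 28.98 = 69 RMB per additional person tested

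**Step 4. Relative inflation.** With other arm cost C and research cost S, the unit cost is multiplied by (C + S)/C. The number of testers cancels. The larger SOC effect in the first row is therefore absolute. In percentage terms SOC is hit harder only if its C is lower.

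**Limit of the illustration.** In the trial 2 pilot, no SOC participant tested (0/5, Table S2). At that rate the SOC cost per person tested is undefined, whatever is counted in the numerator.

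**The case against.** The case on the other side has four parts.

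**The platform also delivers the service.** It takes kit orders and result uploads, and Table S1 lists voluntary reporting of results under intervention delivery. This stands. Part of the coordination cost may be a genuine delivery cost, so one cannot infer that every unit cost is inflated. Mixed use calls for a split, however. It does not justify counting the whole.

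**The arm effect depends on allocation.** A reader might infer that the rule necessarily penalises SOC and gives HCVST a false cost advantage. The Protocol does not support that. It states no allocation rule, the ordering reverses if the cost is charged to HCVST, and equal costs drop out of the ICER. An equal split is natural for survey use, since both arms have 42 participants and complete the same surveys, but it remains an assumption.

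**Participant payments are not listed as costs.** The Protocol pays for both surveys ("After completing the survey, participants will receive 20 RMB (approximately 3 USD"; "Participants will receive 30 RMB (approximately 4 USD) for the follow-up survey"). The opening of the variable-cost definition, "Variable costs refer to the cost which are expenses that vary with the number of participants used", might suggest that these payments count. The sentence goes on to name kits, postage and other consumables, and Cost data does not list participant payments either. They should not be treated as a planned arm cost. Nor does the 5 RMB photo payment help the argument: a person counts as tested only after submitting a photo, so it would add about the same per counted tester in both arms.

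**Line-item costing belongs in a later plan.** This is fair for missing detail, and the examples in both sections are illustrative. But the Economic evaluation paragraph does more than leave detail open. It states an inclusion rule and names a survey item under it.

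**Conclusion.** The point holds as an inconsistency between the stated provider perspective and the stated definition of start-up cost. Following the Analysis plan literally would bring research-only survey set-up into the cost per person tested and per person diagnosed, and would raise both to the extent that such cost is present.

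The overall size cannot be determined from the Protocol. The figures of 238 against 57 or 30 RMB are per 1,000 RMB of research cost per arm. They rest on an equal split, full enrolment of 42 per arm, and the design or pilot testing rates. They show sensitivity and do not estimate a bias. Under the equal split the ICER is unaffected; under an unequal split it moves. The primary outcome is not touched. This is a correction to a secondary economic analysis, worth making because it is cheap and can be settled before costs are collected.

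**What to change.** Amend Cost data and the Economic evaluation paragraph together so that they give one definition.

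1. Limit the numerator to resources a provider needs to deliver each arm.
2. Replace survey-platform coordination in the start-up definition with the delivery share of the platform: kit ordering charged to HCVST, and result return charged to both arms if it is treated as part of the service.
3. Exclude survey use of the platform (eligibility, baseline and follow-up).
4. State that the 20 and 30 RMB survey payments are not arm costs.
5. State how any remaining shared cost is divided between arms.
6. Report research-inclusive costs only as a sensitivity analysis.

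The cost is a few sentences of wording and a little more costing work. The one small downside is that the platform cost has to be divided between survey and delivery use by a stated assumption.

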**Background**

HCV is a public health concern with a global goal to be eliminated by 2030 set by World Health Organization (WHO)[1]. In 2019, there were 58 million people with chronic HCV infection globally, but only 21% were diagnosed[1]. Untreated HCV infection can lead to death due to liver cancer, fulminant hepatitis, liver cirrhosis and other complications[1]. MSM are disproportionately affected by HCV infection[2], especially HIV-positive MSM with high-risk behaviors such as condomless anal sex or injection drug use [3]. A global systematic review found the prevalence of HCV in MSM living with HIV was 6.3% (95% CI: 5.3 to 7.5) compared to 1.5% (95% CI: 1.0 to 2.1) in HIV-negative MSM[4]. In China, a meta-analysis estimated that HCV prevalence was 1.2% and 8.4% among general MSM and MSM living with HIV, respectively[5].

Expanding HCV testing is critical for HCV control[3]. WHO recommends all MSM should receive HCV testing at least once every year[6]. Studies suggest that only 41% of Chinese MSM have been tested for HCV in their lifetime[7], which was 49% lower than WHO’s target[8]. Previous studies showed that perception of HCV as low risk and fear of stigma and discrimination from health care providers contributed to the low uptake of HCV testing among MSM[9]. Additionally, inconvenience and lack of privacy for facility-based HCV testing, unlinked systems for HIV and other STDs, and COVID-19 restrictions also led to low HCV testing uptake [10, 11]. In response to these gaps, the latest guideline from WHO strongly recommends HCVST as a potential method to enhance uptake of HCV testing among MSM[12].

HCV self-testing (HCVST) is a process in which an individual collects their specimen (blood or oral fluid), performs a simple rapid diagnostic test, and then interprets their result in a private setting, either alone or with someone they trust[12]. Several studies in Egypt[13] and Vietnam[14] have demonstrated high usability, acceptability and feasibility of using HCVST among MSM, which provides a strong foundation to support the promotion of HCVST.

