***Secondary outcomes***

We will additionally look at the incremental benefit of HCVST efficacy in promoting HCV testing, number of newly identified cases of HCV, the linkage to HCV clinical care after self-testing, and HIV, chlamydia and gonorrhea testing within four weeks.

We will examine cost-effectiveness alongside the trial. Using a decision-tree model, we will calculate the cost per person tested for HCV (includes both self-testing and facility-based testing), cost per person self-tested for HCV, cost per person tested for HCV in a facility, and cost per person diagnosed with HCV. We will also examine the incremental cost-effectiveness ratio comparing the two arms of the trials. We will conduct deterministic univariate sensitivity analyses and probabilistic sensitivity analysis to examine the robustness of our findings.

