***Sample size***

Sample size was calculated using Fisher’s exact test for two proportions using estimates from initial pilot study data (*n*=50 participants) in SAS version 9.4 (SAS Institute, Cary, NC, USA). Two of the 50 participants were not included in the estimates since they did not provide one-month follow-up data. In trial 1 (HIV-negative MSM), the HCV testing rate in the HCVST arm and in the SOC arm was 78.9% and 10.5%, respectively. In trial 2 (MSM living with HIV), the HCV testing rate in the HCVST arm was 40.0%, and no participants in the SOC arm received testing for HCV.

For sample size calculations, we assumed equal sample sizes in HCVST and SOC (i.e., 1:1 allocation ratio), 90% power, significance level of *α*= 0.05, two-sided testing, and 20% loss-to-follow-up (LTFU). The estimated required sample size for trial 1 (HIV-negative MSM) was *n*=17 in each arm (*n*=34 total). The estimated required sample size for trial 2 (MSM living with HIV) was *n*=27 in each arm (*n*=54 total).

Since the pilot study was relatively small (*n*=48 evaluable participants, 38 HIV-negative and 10 MSM living with HIV), it is possible that the estimated effect sizes were exaggerated. Since our resources allow, we plan to enroll a sample size of 42 in each arm (*n*=84 total) for trial 1 (HIV-negative MSM) and a sample size of 42 in each arm (*n*=84 total) for trial 2 (MSM living with HIV). Thus, each NGO will enroll 24 participants: *n*=12 to trial 1 (HIV-negative MSM) and *n*=12 to trial 2 (MSM living with HIV). With this sample size and assuming a 10% testing rate in the SOC, we will be 90% powered to detect a difference of approximately 32% or greater in the HCV testing rate between the HCVST and SOC arms.

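### The economic analysis labels each arm's average cost as incremental, and its cost per detected case divides by a count more likely than not to be zero in three of the four arms

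*Protocol*

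**What the plan says.** The Economic evaluation part of the Analysis plan opens with "We will estimate the total unit and incremental unit cost for each arm in two trials". After sorting costs into start-up, fixed and variable, it says that all costs of each arm will be calculated and that "this cost will be divided by the number of MSM tested and the number of newly detected HCV cases in each study arm". The purpose it gives for this division is "to calculate incremental unit costs". It then gives the decision tree the task of examining uncertainty through sensitivity analyses.

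The Secondary outcomes section puts the economic work differently. There the decision tree itself produces the unit costs, among them "cost per person diagnosed with HCV". A between-arm measure is listed separately: "We will also examine the incremental cost-effectiveness ratio comparing the two arms of the trials". No formula is given for it.

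**The concern.** There are two problems.

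1. **The calculation does not give the quantity it names.** Total arm cost divided by that arm's own number tested, or its own number of new cases, is an average cost. An incremental cost compares arms in both numerator and denominator, so it cannot exist for each arm of a two-arm trial. This is also the only economic calculation that the protocol spells out.

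2. **The cost-per-case denominator is a very small observed count.** Arms of 42 men, partial testing and low prevalence leave few infections to find. An arm with no detected case has no observed cost per case.

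Cost-effectiveness is one of the trial's stated purposes. A per-arm average reported as incremental would be read as the price of one additional man tested, which it is not. A cost per case from observed counts would often be missing for one side of the comparison.

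**Working it through.** **Plan's own figures.** The protocol states no expected case count and no cost, so there is no economic figure to reproduce. The sample-size figures that supply the inputs do reproduce with the Walters arcsine approximation to Fisher's exact test, which is assumed to be the SAS method. Trial 1 needs 13 per arm, and 13/0.8 rounds up to 17. Trial 2 needs 21 per arm, and 21/0.8 rounds up to 27. With 42 per arm and 10% against 42%, power is 0.897, which matches the stated 90% for a difference of about 32 points.

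**Step 1: average against incremental.** Let C be an arm's cost and T its number tested.

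- Calculation in the Analysis plan: C_HCVST/T_HCVST and C_SOC/T_SOC, two averages per trial.
- Incremental cost per additional man tested: (C_HCVST − C_SOC)/(T_HCVST − T_SOC), one figure per trial.

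The protocol gives no costs, so this illustration uses assumed ones in arbitrary units, with about 33 and 5 men tested in trial 1:

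| Assumed cost, HCVST / SOC | Average, HCVST | Average, SOC | Incremental |
|---|---|---|---|
| 2000 / 500 | 2000/33 = 60.6 | 500/5 = 100.0 | 1500/28 = 53.6 |
| 2000 / 1000 | 2000/33 = 60.6 | 1000/5 = 200.0 | 1000/28 = 35.7 |

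The incremental figure equals neither average. It also moves with the control arm's cost, which the self-testing average cannot reflect.

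**Step 2: expected cases and the chance of none.** Inputs:

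- Arm size (Sample size): "we plan to enroll a sample size of 42 in each arm", in each trial.
- Testing rates, trial 1 (Sample size): "the HCV testing rate in the HCVST arm and in the SOC arm was 78.9% and 10.5%, respectively".
- Testing rates, trial 2 (Sample size, Table S2): 40.0% (2/5) with self-testing and 0/5 in the control arm. The planning value of 10% is used for the control arm, with 0% as the alternative.
- Prevalence (Background): "HCV prevalence was 1.2% and 8.4% among general MSM and MSM living with HIV". The global review cited there gives 1.5% (upper limit 2.1%) for HIV-negative MSM and 6.3% for MSM living with HIV.

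Formulas: expected cases = 42 × testing rate × prevalence; P(zero) = (1 − testing rate × prevalence)^42.

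| Arm | Expected cases | P(zero) | Other inputs |
|---|---|---|---|
| Trial 1 HCVST | 42 × 0.789 × 0.012 = 0.40 | (1 − 0.00947)^42 = 67% | 61% at 1.5%; 50% at 2.1% |
| Trial 1 SOC | 42 × 0.105 × 0.012 = 0.05 | (1 − 0.00126)^42 = 95% | 94% at 1.5% |
| Trial 2 HCVST | 42 × 0.40 × 0.084 = 1.41 | (1 − 0.0336)^42 = 24% | 34% at 6.3% |
| Trial 2 SOC (10%) | 42 × 0.10 × 0.084 = 0.35 | (1 − 0.0084)^42 = 70% | 77% at 6.3%; 100% at 0/5 tested |

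**Step 3: at least one arm with no case.** P = 1 − (1 − P0_HCVST)(1 − P0_SOC).

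- Trial 1: 1 − (0.329 × 0.052) = 98% (97% at 1.5% prevalence).
- Trial 2 at 10% control testing: 1 − (0.762 × 0.298) = 77% (85% at 6.3%; 100% at the pilot control rate).

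In trial 1 both arms have none in 0.671 × 0.948 = 64% of realisations. A between-arm ratio per observed case would then be undefined as well.

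**The case against.** The strongest reply is that the incremental measure is already planned. Secondary outcomes announces a ratio comparing the arms, and puts cost per diagnosis among the decision-tree outputs. On that view the Analysis plan has one misused word, and model inputs or a rule for zero counts can properly wait for an analysis plan that is not shown here.

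Much of this stands. A reader might infer that the trial has no incremental measure, or that its cost-effectiveness answer must come out wrong. The documents do not support either: nothing says that the per-arm averages will serve as the between-arm ratio. What remains is that the one calculation written down carries the wrong name, and that the two sections differ on where cost per case comes from. One uses the tree as the calculator; the other uses observed counts and keeps the tree for uncertainty.

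Three other inferences go too far:

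- **The error reverses the sign of the result.** That would need the difference between two averages to be set against an incremental ratio, and the protocol never plans to subtract the averages. When more men are tested under self-testing and its average cost is the lower one, the incremental ratio lies below that average (53.6 < 60.6 < 100.0 in the illustration). The two agree in direction.
- **Cost per man tested is likely to be undefined in the trial 2 control arm.** The pilot rate of zero rests on five men. At the planned 10%, the chance of no tester among 42 is 0.9^42, about 1.2%.
- **Zero cases is the usual result in every arm.** It is not in the trial 2 self-testing arm, where the chance is 24% to 34%.

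It is also fair that 1.2% describes MSM in general, whereas eligibility requires a recent risk factor. At 2.1% the trial 1 self-testing arm is close to an even chance.

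**Conclusion.** The point holds in this form. The Analysis plan mislabels average costs as incremental, and its instruction for cost per case conflicts with Secondary outcomes. At the documents' central inputs, an observed cost per case is more likely than not to be undefined in three of the four arms, and at least one arm is without a case in most realisations of each trial.

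The probabilities assume that the cited prevalences apply to the men who test, that every infection counts as new, that the test finds every infection, and that nobody is lost to follow-up. Losses or the exclusion of known infections would raise the chance of zero. For example, removing 21% of infections (the global diagnosed share in Background) gives 32% to 43% in the trial 2 self-testing arm, still below half. A higher prevalence in this risk-selected population would lower it. The label error rests on none of these assumptions.

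The primary outcome and its analysis are unaffected. The correction should be made because it concerns a stated aim and costs very little.

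**What to change.** Make three changes in the economic text:

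1. In the Analysis plan, call the per-arm quotient the average cost per person tested, and drop the promise of an incremental figure for each arm.
2. In Secondary outcomes, define the incremental cost-effectiveness ratio as (cost HCVST − cost SOC)/(number tested HCVST − number tested SOC), one per trial, with its uncertainty from the probabilistic analysis already planned. Differences in number tested can be used directly because the arms are of equal size.
3. In both sections, state that cost per case detected comes from the decision tree, with prevalence, kit accuracy and the trial's testing rates as inputs. Report the observed case counts descriptively, by arm.

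This takes two or three sentences and needs no further participants, data or models. The drawback is that cost per case then depends on the modelled prevalence. The prevalence source should be named and varied in the sensitivity analyses; the Background values (1.2% to 2.1% and 6.3% to 8.4%) offer a starting range.
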